#### Student Practice Evaluation Form-Revised

Whether students pass their placement will be assessed using the Student Practice Evaluation Form-Revised (SPEF-R). The SPEF-R is a standardised and validated instrument used to assess professional competencies of occupational therapy students [31]. It is routinely used across Australia and is completed by a clinical supervisor to assess students’ practice competencies. The SPEF-R was first developed in 2004 and revised in 2011, and further validation research has been undertaken to establish the psychometric properties of the tool [32]. The SPEF-R is suitable for evaluating students in a wide range of placement settings, including health (acute, rehabilitation and community services including physical medicine and mental health) and education, and for placements involving paediatric or adult clients. It allows for the assessment of a broad range of skills and competencies.

Student performance is usually evaluated across eight domains in the SPEF-R; however, only the first four will be used in this study. Use of an approved modified version of the SPEF-R is common when assessing students in foundation/early years of their programs, as the placement hours are often fewer (e.g. 1 week rather than 6 weeks) and the competencies required of students more limited. The four domains of interest in this trial are:Professional behaviour: *conducts self in a professional manner*, assessed using five items, of which four are core items that must be passedSelf-management skills: *demonstrates effective self-management skill,* assessed using five items, of which two are core and a further two are required to achieve a pass in the domainCo-worker communication: *communicates effectively within the workplace,* assessed using three items, of which two are core and must be passedCommunication: *communicates effectively with service users and significant others,* assessed using five items of which four core items must be passed

Each SCP and TCP student will be evaluated by their clinical supervisor across the four SPEF-R domains of interest. Each student will also complete a matching SPEF-R in a reflective, self-assessment mode, before receiving final feedback from their clinical supervisor. The SPEF-R allows for the inclusion of written comments. Assessors of student performance using the SPEF-R cannot be blinded to group allocation of the student, as they must have observed the student on placement.

Individual student performance on each item is rated on a 5-point scale as follows: 1. *Performs unacceptably*; 2. *Experiencing difficulty or performs marginally*; 3. *Performs adequately*; 4. *Performs proficiently*; and 5. *Performs with distinction*. Scores of 1 or 2 indicate a failing performance. Students must pass all core units in each of the four domains of the SPEF-R to achieve an overall pass in the placement. Data will be collated to determine whether students pass overall, which domains are passed and the sum of the individual item scores in the SPEF-R. The frequencies of items identified as *not applicable* and *insufficient observation* in the SPEF-R will also be determined for each student. The student and supervisor reports of comparable learning experiences in each placement setting will be compared using data extracted from the SPEF-R and a self-report survey (research question 4).

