## Discussion

The use of simulation in health-related fields like occupational therapy is not unusual, but simulation typically relates to specific activities. For example, a simulated client might be hired for students to take turns to interview, or learning activities might be held in a mock kitchen. The simulation described here is innovative in that it encapsulates a 5-day block of integrated activities, designed and delivered in a manner that aims to emulate best-practice placement experiences. This simulation is designed to replicate, and potentially replace, a short-duration traditional placement experience.

A quality traditional placement experience would comprise a range of activities for the student to participate in, roles for the student to try out and a variety of clients and professionals for the student to engage with, all in a well-supported environment [8, 9]. Despite the best of intentions, not all traditional placements will, in reality, provide this experience for students [38]. Placements might occur at a quiet time in the organisation; the supervisor may need to undertake a range of desk-top tasks in which it is difficult to engage the students; or the student’s placement experience may, for many reasons, not be the priority for the supervisor or organisation at that particular time. One important advantage of the SCP is the consistency of the content and delivery experience, and therefore the likelihood that all students will be exposed to a particular set of experiences that can lead to achieving the desired learning outcomes.

A second innovation in this study is the inclusion of the economic evaluation. The comparison of student learning and student evaluations of their experience will speak to whether the SCP is as effective as the TCP. Economic evaluation will provide valuable information about the efficiency of offering block simulation as an integral (and integrated) component of allied health courses, to partially meet the professional practice experiences required for accreditation. The economic evaluation has been carefully designed to capture all costs of providing both the SCP and the TCP. These costs are not typically transparent, and this information will be very useful to the occupational therapy profession, universities and the health and human services sector who host placements. The cost collection will also help to address the question of affordability.

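### The SPEF-R total is defined as a sum of item scores although items may go unrated, so totals are not comparable between students with different numbers of rated items

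*Protocol article*

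**What the plan says.** The section Student Practice Evaluation Form-Revised limits the form to four of its eight domains and gives the number of items in each. On scoring it states: "Individual student performance on each item is rated on a 5-point scale as follows", and then lists ratings from 1 to 5, of which 1 and 2 are failing. Neither *not applicable* nor *insufficient observation* has a numeric value. Three results are to be derived for each student: overall pass, the domains passed, and "the sum of the individual item scores in the SPEF-R". The next sentence reads: "The frequencies of items identified as *not applicable* and *insufficient observation* in the SPEF-R will also be determined for each student".

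The article gives no proration, no averaging over rated items and no minimum number of rated items. Research question 2 (Aims and research questions) asks whether the frequencies of unrated items are similar in the two placement types. Statistical analyses methods compares them between arms with a *t* test and 95% confidence intervals.

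**The concern.** A sum is a fair summary only if every student is scored on the same number of items, and here the article itself expects that they will not be. Two students who perform equally well can then have different totals because one supervisor had fewer occasions to rate.

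The same holds between arms. The trial asks whether unrated items are equally common in SCP and TCP. If they are not, the total carries that difference as though it were a difference in competence. A reader of the results could not tell from the total alone which of the two had been found.

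**Working it through.** The article states no figure for this total, so there is none to reproduce. Its sample size concerns the examination and plays no part here.

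**Inputs from the section Student Practice Evaluation Form-Revised**
- Items per domain: 5, 5, 3 and 5, so 5 + 5 + 3 + 5 = 18.
- Rating per item: 1 to 5, so the total with all items rated runs from 18 × 1 = 18 to 18 × 5 = 90.
- An unrated item has no score. Read literally, it adds nothing to the sum.

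**Effect on one student.** With a constant rating *r* and *k* unrated items, the sum is *r* × (18 − *k*) and the proportion lost is *k*/18.

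| Rating throughout | All 18 rated | 1 unrated | 2 unrated |
|---|---|---|---|
| 3 | 54 | 51 | 48 |
| 4 | 72 | 68 | 64 |
| Proportion lost | 0 | 1/18 = 5.6% | 2/18 = 11.1% |

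The ranking can also reverse. A student rated 4 on every observed item, with five items unrated, totals 4 × 13 = 52. A student rated 3 on all 18 items totals 54.

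**Effect between arms.** Suppose true performance is equal and items go unrated regardless of how the student would have been rated. The spurious gap is then the mean rating times the difference in the mean number of unrated items. The article gives neither quantity, so the following values are assumptions. Ratings of 2, 3, 4 and 5 have probabilities 0.05, 0.40, 0.40 and 0.15, and the mean is 0.10 + 1.20 + 1.60 + 0.75 = 3.65.

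| Assumed unrated rate, SCP v TCP | Mean total, SCP v TCP | Gap | Mean of rated items |
|---|---|---|---|
| 5% v 5% | 62.4 v 62.4 | none | 3.65 v 3.65 |
| 5% v 5% on average, more variable in TCP | 62.4 v 62.4 | none | 3.65 v 3.65 |
| 2% v 10% | 64.4 v 59.1 | 5.3 towards SCP | 3.65 v 3.65 |
| 10% v 2% | 59.1 v 64.4 | 5.3 towards TCP | 3.65 v 3.65 |

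Check of the third row: 18 × 3.65 × 0.98 = 64.4 and 18 × 3.65 × 0.90 = 59.1. Equivalently, 18 × (0.10 − 0.02) = 1.44 more unrated items in TCP, and 1.44 × 3.65 = 5.3 points.

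Two things follow. The gap depends on the difference in the *mean* number of unrated items, so more variable exposure in one arm is not enough to produce it. The mean of rated items shows no gap in any of these cases.

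**The case against.** **No planned analysis uses the total.** Statistical analyses methods analyses overall pass/fail by logistic regression, domain pass/fail by chi-square and single items by Mann-Whitney. The criterion of more than 1 point is on the 5-point item scale. The total has no test and no margin. This stands, and it limits the consequence.

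**The scoring rule may be elsewhere.** The form is a standardised instrument, and its manual or the analysis plan may say how unrated items are handled. This stands in part. A fuller rule could exist, but the rule printed in the article is a sum, and it sits beside a sentence that expects unrated items.

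**A reader might infer that the total is biased towards SCP and so helps a non-inferiority claim.** The Discussion invites this. It says of traditional placements "Despite the best of intentions, not all traditional placements will, in reality, provide this experience for students", and of the simulated placement "One important advantage of the SCP is the consistency of the content and delivery experience". But these remarks concern placement activities in general and say nothing about SPEF-R items. Research question 2 leaves the frequencies open. Other features point the opposite way: one SCP supervisor has 9 or 10 students (The SCP intervention), while TCP students are placed singly or in pairs (The TCP comparison group), so insufficient observation could be commoner in SCP. With no test of the total, no planned non-inferiority conclusion depends on it either.

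**A reader might also infer that an unrated core item blocks a pass.** The article requires core items to be passed, but it defines failing as a rating of 1 or 2 and does not say how an unrated core item counts. That is silence which the manual or analysis plan may fill, not a stated error.

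**Conclusion.** The point holds as a defect in how one secondary score is derived. As written, the SPEF-R total is not comparable between students with different numbers of rated items. Each unrated item costs the rating it would have had, which is 5.6% of the sum for a student rated at a constant level. This rests on the literal reading that unrated items contribute nothing.

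Whether the arms would differ, by how much and in which direction cannot be told from the article. The gap of 5.3 points follows from assumed rates of 2% and 10% and illustrates the mechanism; it is not an estimate. Bias towards SCP and spurious failures are not established. The examination outcome and the item-by-item comparisons are unaffected by the summing. The point is minor, but the remedy is simple enough that it should be adopted.

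**What to change.** Replace the sum by the mean of the rated items, on the 1 to 5 scale, or by a prorated sum (18 times that mean). Set in advance the minimum number of items that must be rated for a student to have a score; 14 of 18 would be one possible choice. Report the score by arm beside the counts of *not applicable* and *insufficient observation* items already planned, together with the number of students below the minimum.

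The mean of rated items treats the unrated items as if they would have been rated like the others. If particular items are left unrated far more often in one arm, the planned item-level results should be read alongside it.

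The cost is one derivation rule. The item ratings and unrated-item counts are already to be collected, so no new data, visits or sample are needed.

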#### Unit grade

The overall grade for the unit of study will be collected for each participating student and will be reported using a continuous scale ranging from 0 to 100%. A mean difference of ≥7 points on the subject/unit grade between groups will be considered an educationally meaningful difference. This difference was selected as meaningful because it represents ≥50% of each passing grade scale (e.g. Pass = 50–65% in some universities and 50–60% in others), and a difference of 7 points is likely to result in a shift in the allocated grade for a student.

#### Economic data collection

To assess cost-effectiveness of SCP in comparison to TCP, data on resource use will be collected. For SCP the opportunity cost of accommodation (e.g. simulated office, tutorial rooms) and other capital costs (e.g. equipment, databases developed specifically for simulation practices), repair and maintenance will be collected. Staff time will be estimated with information about activities undertaken to deliver both the SCP and TCP. Activities that are undertaken before the placement, including time used in preparation for the SCP and time used to secure a TCP, will be included. Time spent on these activities will be multiplied by the corresponding hourly rates and adjusted for overheads. The cost of developing the SCP materials and financial reimbursement to TCP providers will also be collected. Purpose-built cost templates will be used to collect these data from the appropriate sources within each university.

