### Aims and research questions

The study aims to explore the differences between a 40-hour block SCP experience and a 40-hour block TCP experience in terms of development of professional competencies and fieldwork confidence, and to determine the comparative delivery costs for the SCP and TCP programs as borne by the university.

The research questions are:Do students who undertake an SCP in the early years of an entry-level occupational therapy program achieve *non-inferior outcomes* in their development of professional practice skills compared with those who attend a TCP, as assessed by a post-placement written examination (primary outcome), Student Practice Evaluation Form-Revised (SPEF-R) evaluation [31, 32] and end-of-semester study unit score?Do students and supervisors report similar professional practice learning opportunities when students complete an SCP compared to those students who complete a TCP, assessed using a self-report survey, and similar frequencies of *not applicable* and *insufficient observation* items in the SPEF-R?Economic research questions: If non-inferiority is established, does SCP cost less than TCP from the perspective of (1) the health sector and (2) the universities as providers?If costs of SCP are not less than those of TCP, are there offsetting benefits which still make the SCP value for money?
Do students who experience an SCP in the early years of an entry-level occupational therapy program report self-confidence outcomes that are non-inferior to those who attend a TCP, as measured by the Student Confidence Questionnaire [33]?What are the perceptions of quality and adequacy of the TCP versus SCP experience of students and clinical educators?

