### Instruments and measures

Outcomes will be assessed using a variety of tools to gather both qualitative and quantitative data to address the research questions. Data will be collected immediately prior to or at the beginning of placement, on completion of placement and at the end of the unit of study (see Table 2). Demographic data including student age, gender, university, prior qualifications and prior placement experience will also be collected.

**Table 2 Tab2:** Description of the instruments used to collect data across the trial

Instrument	Type	Timing	Respondent
SPEF-R	Paper-based	Complete across placement week, finalising during morning of 5^th^ day of placement	Clinical supervisors
SPEF-R, self assessment	Paper-based	Complete across placement week, finalising during the 5^th^ day of placement	Students (self-report)
Pre-placement questionnaire	Paper-based	Pre-placement briefing 1 week prior to placement *Or* morning of 1^st^ day of placement	Students (self-report)
Post-placement questionnaire	Paper-based	Afternoon of 5^th^ day of placement	Students (self-report)
SPEF-R, student review	Paper-based	Complete across placement week, finalising during the afternoon of 5^th^ day of placement	Students
Examination	Paper-based	Within 4 weeks of placement conclusion	Students
Sessions evaluation	Online	Within 2 weeks of placement conclusion	SCP students only
Focus group feedback	Transcribed audio	Within 4 weeks of placement conclusion	Students Clinical educators
Clinical educator survey	Online	Within 2 weeks of placement conclusion	Clinical educators (clinical supervisors and simulation facilitators)
Cost data collection	Digital	Across the full extent of the trial	Partner university site coordinators, investigators, placement support staff and project support staff

*SPEF-R* Student Practice Evaluation Form-Revised

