### Ethical considerations

To support implementation, the design of the trial ensured there was no disincentive for students to participate. All university partners have adjusted curricular requirements for the particular unit of study in which the program will be situated so that all students can be allocated to either the SCP or TCP. In addition, data collection instruments are aligned to usual educational practices and ordinary performance assessment wherever possible. These adjustments have been considered by relevant curriculum authorities in each university (for example, an Academic Program Standing Committee) to ensure pedagogical integrity. Student assignment to the placement mode will be on the basis of random allocation, regardless of their decision to take part in the study. Eligible students will be provided with the opportunity to volunteer to participate in the study; the only difference between those participating and those not will be an agreement to allow data collected as part of the placement activity to be included in the trial. Student participants will not be incentivised or compensated, and there is no advantage to participating, or disadvantage to non-participation.

Clinical supervisors, for both SCP and TCP, and the educators who help to deliver the SCP program will also be invited to participate by contributing data. The SCP supervisors and educators will be paid for their time but will not be incentivised or additionally compensated for agreeing to contribute data to the study. The TCP supervisors undertake the student supervision role within their organisations in the usual way and receive no individual payment. Some organisations charge for student placement days, and where those agreements are in place, payments to organisations will be made in the usual way and this data collected as part of the economic component of the trial.

All participants (students, clinical supervisors, simulation facilitators) can elect to withdraw from participation in the study in part or in full, but still participate in the SCP or TCP activities. All data about and from students will be labelled with the student’s institutional student number but not their name. This ensures that the various items of data, which might be submitted separately and across a span of several weeks, can be matched to particular students, but that personal details, such as the students’ names, are kept separate from the data files.

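### The economic question includes the health-sector perspective, but the aim and the named cost sources cover only the university, so the host's TCP supervision cost has no stated source

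*Protocol article*

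**What the plan says.** Under Aims and research questions, the article sets out to determine the "comparative delivery costs for the SCP and TCP programs as borne by the university". The economic research question in the same section is wider. It asks, if non-inferiority is established, "does SCP cost less than TCP from the perspective of (1) the health sector and (2) the universities as providers".

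Economic data collection describes what is gathered. "Staff time will be estimated with information about activities undertaken to deliver both the SCP and TCP"; that time is then valued at hourly rates with an adjustment for overheads. Reimbursement paid to TCP providers is also recorded. On sources, the section says: "Purpose-built cost templates will be used to collect these data from the appropriate sources within each university". Table 2 (Instruments and measures) gives the respondents for the cost data as "Partner university site coordinators, investigators, placement support staff and project support staff".

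Ethical considerations describes the two supervision arrangements. SCP supervisors and educators are paid. For the other arm, "The TCP supervisors undertake the student supervision role within their organisations in the usual way and receive no individual payment". Some host organisations charge for placement days, and those payments are recorded.

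The Discussion then states: "The economic evaluation has been carefully designed to capture all costs of providing both the SCP and the TCP".

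**The concern.** The three elements that should agree on perspective do not. The question reaches to the health sector, the aim stops at the university, and the cost respondents are all on the university or project side. A university-side respondent can report what the university spends and what its own staff do. How many hours a host's supervisor gave to a student is known first-hand only in the host organisation.

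Two things are at stake. First, a conclusion about the health sector would be drawn without a stated measure of what the hosts put in. Second, the sign of the cost difference determines the analysis. Under Economic evaluation, a non-inferior and cheaper SCP leads to cost-minimisation, while a non-inferior but dearer SCP leads to cost-effectiveness ratios on longer-term benefits. If TCP cost is understated, SCP looks relatively dearer, and the evaluation could take the second branch where full costing would have taken the first.

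**Working it through.** The article states no cost or host-hours figure, so there is nothing to reproduce. The check sets the statements side by side and then asks whether the gap could matter.

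**Coverage of host supervision time**

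- *Question:* health sector and universities, so host time is in scope.
- *Aim:* university only, so host time is out of scope.
- *Cost templates:* sources inside each university.
- *Table 2, cost row:* university and project staff. The same table names clinical educators as respondents for their survey and the focus groups, but not for cost data.
- *Educator survey (Placement experience):* modelled on the students' experience questions with 5-point agreement ratings. As described, it records perceptions and not hours.
- *Fees:* recorded where charged. A fee is an outlay for the university and income for the host. It does not measure the host's resource use, and where no fee is charged it gives no information.
- *Pathway analysis (Economic evaluation):* sets out the activities in both arms, but names no host-side respondent for the time spent.

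So no named source directly measures host supervision time.

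**Could it matter?**

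Formula: supervisor hours per student = supervisor hours per placement / students per supervisor.

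SCP inputs: 40 hours and a ratio of 1 to 9 or 10 (The SCP intervention).
- 40/10 = 4.0 and 40/9 = 4.4 hours per student. Simulation facilitators are not included, so total SCP staff input is higher.

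TCP inputs: 40 hours, with students placed singly or in pairs (The TCP comparison group). Host hours per placement are not given. The values below are assumptions, and 40 is the ceiling, with a supervisor present throughout.

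| Assumed host hours per placement | Pair (÷2) | Single (÷1) | 212 TCP students |
|---|---|---|---|
| 10 | 5 | 10 | 1,060–2,120 h |
| 20 | 10 | 20 | 2,120–4,240 h |
| 40 | 20 | 40 | 4,240–8,480 h |

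The 212 is half of the planned 425. The matching SCP total is 212 × 4.0 to 212 × 40/9, about 848 to 942 hours.

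Break-even: host time per student equals SCP supervisor time per student at 4.0–4.4 host hours for a single placement, or twice that, 8.0–8.9 hours, for a pair. Above this, the TCP supervision input is the larger of the two; below it, the smaller. The article gives nothing to show which side the true value lies on.

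**The case against.** The strongest reply is that the plan values time by activity and not by payment. Staff time is to be estimated for delivering both programmes, and the pathway analysis is to specify activities in both arms. A reader might infer from the unpaid status of TCP supervisors that their time is costed at zero. The article does not say that, and lack of payment does not imply it under an activity-based method. University placement staff could supply estimates of host time, and the cost templates, which are not shown, may ask for them. It would also go too far to say that the health-sector question cannot be answered.

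Three further points limit the claim.

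- *Perspectives can be mixed up.* Setting paid SCP hours against unpaid TCP hours compares across payers. SCP supervision is paid for within a university-delivered programme, so on a strict health-sector view it would not obviously count, and fees would be income to hosts. The hours above show materiality only; they are not a health-sector cost comparison.
- *Not every host is in the health sector.* The Background lists schools, private practices and other organisations among TCP settings.
- *The size cannot be pinned down.* If one assumed that 10–25% of the 20–40 hour ceiling displaced service, the result would be 2 to 10 hours per student (0.10 × 20 to 0.25 × 40). The low end is below the SCP figure of 4.0–4.4, so it cannot be said that the uncounted time matches or exceeds SCP supervision.

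What remains is a stated mismatch and not merely missing detail. The article positively lists who reports costs, and no host is among them.

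**Conclusion.** The point holds as an inconsistency of perspective. The economic question includes the health sector, while the aim and the named cost sources are confined to the university and the project. Followed as written, the health-sector answer would be incomplete or would depend on proxies that the article does not state, and the Discussion's claim that the costing is complete is not supported.

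The likely direction is that TCP cost is understated. This assumes that hosts spend some supervision time that fees do not cover. The size is unknown; the only bounds are 4.0–4.4 supervisor hours per SCP student and a ceiling of 20–40 per TCP student. The article supports neither a valuation of zero nor a definite reversal of the cost comparison. The primary outcome and the university-perspective cost comparison are not affected.

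**What to change.** Choose one of two routes.

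1. *Narrow the question.* Restrict the economic question and its conclusion to the university perspective, and withdraw the Discussion's claim of complete costing.
2. *Keep the health-sector perspective.* Cost host supervision from a stated proxy, hours per placement × hourly rate plus overheads, using the valuation already planned. Use host-reported hours where they can still be obtained. Treat fees as transfers, and state which hosts count as health sector. Give a sensitivity range for host hours, and report whether the choice between cost-minimisation and cost-effectiveness ratios changes within it.

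Either way, align Aims and research questions, Table 2, Economic data collection and the Discussion.

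Trial status reports that data collection was complete when the article was accepted. New items in the educator survey, due within 2 weeks of placement, are therefore no longer a dependable remedy, and any hours obtained now would be retrospective and voluntary. The first route costs only a narrower conclusion. The second costs some analysis time and gives a proxy-based estimate with wider uncertainty.
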